## Abstract

**Background:**

The risk of cardiovascular events remains high in patients with coronary heart disease (CHD) after successful percutaneous coronary intervention (PCI). *Panax quinquefolius* saponin, a major component of Xinyue capsule, has been used to treat patients with CHD. The aim of this study is to evaluate the efficacy and safety of Xinyue capsules in patients with CHD after PCI.

**Methods/design:**

This study is a multicenter, placebo-controlled, double-blind, randomized controlled clinical trial. A total of 1100 participants are randomly allocated to two groups: the intervention group and a placebo group. The intervention group receives Xinyue capsules plus conventional treatment, and the placebo group receives placebo capsules plus conventional treatment. The patients receive either Xinyue or placebo capsules three times daily (1.8 g/day) for up to 24 weeks. The primary outcome measure is the time from randomization to the first occurrence of major adverse cardiovascular events. The secondary outcome measure is the time from randomization to the first occurrence of stroke, pulmonary embolism, and peripheral vascular events, as well as death due to any cause. All outcome measures will be assessed at 12, 24, 36, and 48 weeks after randomization. Adverse events will be monitored during the trial.

**Discussion:**

The aim of this study is to evaluate the effects of Xinyue capsules on patients with CHD after interventional treatment. The results of this trial will provide critical evidence regarding Chinese herbal medicine treatment for CHD.

**Trial registration:**

Chinese Clinical Trials Registry identifier ChiCTR-IPR-14005475. Registered on 10 November 2014.

**Electronic supplementary material:**

The online version of this article (doi:10.1186/s13063-016-1531-x) contains supplementary material, which is available to authorized users.

## Background

Percutaneous coronary intervention (PCI) is commonly performed for coronary revascularization in patients with stable angina or acute coronary syndrome (ACS) [1]. Nevertheless, there are several medications with proven benefit to patients with cardiovascular disease, such as dual-antiplatelet therapy, statins, β-blockers, and angiotensin-converting enzyme inhibitors [2]. Unfortunately, the risk of cardiovascular events remains high in patients after PCI [3]. Many patients do not receive the conventional treatment due to the side effects, contraindications, and drug-drug interactions [4]. Selecting the optimal clinical strategies to prevent the occurrence of cardiovascular events is challenging.

Traditional Chinese medicine (TCM) has been used to treat coronary heart disease (CHD) for thousands of years [5]. From the perspective of TCM, patients with CHD can be divided into different syndromes (i.e., different *zhengs*). In the diagnosis of CHD, the “Qi and Yin inadequacy syndrome” is the important subtype. In 2005, Xinyue capsules were approved by the China Food and Drug Administration for treatment of CHD. The main component of Xinyue capsules—*Panax quinquefolius* saponin (PQS)—is extracted from the stem and leaves of *Panax quinquefolium*, which in TCM theory could reinforce Qi and nourish Yin. Previous studies have shown that PQS has various pharmacological actions, including anti-myocardial cell damage [6], protection of heart function, reduction of myocardial oxygen consumption [7, 8], improvement of myocardial perfusion [9] and ventricular remodeling after acute myocardial infarction (MI) [10], antiapoptosis of ischemic myocardial cells [11, 12], regulation of glucose and lipid metabolism [13], and improvement of insulin resistance [14, 15]. A multicenter randomized clinical study [16] showed that the combination of Xinyue capsules with Chuanxiong capsules and conventional Western interventions could reduce the occurrence of cardiovascular events in patients with ACS after PCI without increasing the risk of major bleeding. The results of pharmaceutical chemistry and pharmacokinetics conducted jointly by Xiyuan Hospital and Medical University of Vienna showed that the fingerprint of Xinyue capsules from different batches or the same batch at different time points was consistent, and the measurements of heavy metal and pesticide residues were within European Union standards.

Based on the multifactorial effect on CHD of Xiyue capsule, our hypothesis is that Xiyue capsules plus conventional treatment can improve cardiovascular outcomes in patients with CHD after interventional treatment compared with conventional treatment alone. If successful, it will provide a novel, promising alternative strategy for further reducing cardiovascular events.

## Methods/design

### Study design

This study is registered in the Chinese Clinical Trials Registry (ChiCTR-IPR-14005475). It is a multicenter, double-blind, randomized, placebo-controlled clinical trial. This study complies with the principles of the Declaration of Helsinki and Good Clinical Practice guidelines. Written informed consent will be obtained from all patients prior to their participation in this study, and the recruited patients will be randomized to either the Xiyue capsule group or the placebo group. We will rigorously follow the Consolidated Standards of Reporting Trials (CONSORT) recommendations in reporting the results [17].

The trial will be conducted in 25 centers in China (see in ​Additional file 1). A total of 1100 participants will be recruited. After acquiring consent from the participants or their parents and/or legal guardians, the participants will be enrolled in the trial, which consists of a 1-week run-in period, a 24-week treatment period, and a 24-week follow-up period. An outline of the study procedures is illustrated in Fig. 1.

**Fig. 1 Fig1:**
[figure not shown]
Study flowchart. *QOLQ* Quality of Life Questionnaire, *SF-36* 36-item Short Form Health Survey, *TCM* traditional Chinese medicine

### Participants

Inpatients and outpatients in the participating centers will be screened if they meet the selection criteria.

#### Inclusion criteria

CHD was diagnosed according to the guidelines [2, 18]. All participants must have received successful PCI.The time window is within 1 year after PCI and the patient must be clinically stable, defined as follows:No progressive chest pain is present.The troponin value is within normal range or slightly elevated, but lower than the 99th percentile of the upper reference limit value.The participants must have a Canadian Cardiovascular Society classification of angina I to IIPatients are diagnosed as having a syndrome of deficiency of both Qi and Yin according to TCM standards [19].Patients must be aged 18–75 years.Patients must have a New York Heart Association cardiac functional class I–IIPatients are informed about the trial and voluntarily sign the consent form.

#### Exclusion criteria

Renal insufficiency, male serum creatinine >2.5 mg/dl (>220 μmol/L), female serum creatinine >2.0 mg/dl (>175 μmol/L)Serious liver disease or alanine transaminase and aspartate transaminase values two times higher than the upper reference limit valueSystolic blood pressure >160 mmHg or diastolic blood pressure >100 mmHgPresence of diabetes with random blood glucose level ≥13.7 mmol/L or HbA1c ≥9.5 %Pregnant women or women who are preparing for pregnancy, and subjects who are known to be allergic to ingredients of the study drugAcute cerebrovascular diseaseMalignancy or having a life expectancy less than 3 yearsSevere hematopoietic diseasesSevere psychiatric conditions Previous involvement in other clinical trials or participation in other clinical trials within the past 3 months

### Withdrawal, dropout, and discontinuation

Participants can voluntarily withdraw at any time during the trial. Subjects who meet the inclusion criteria, fill out and sign the consent form, and successfully enter the randomized trial who fail to complete the observational period proposed in the trial, regardless of time and reasons, are considered as dropout cases. Reasons for withdrawal will be recorded in case report forms (CRFs), and the last data recorded for these participants will be included in the data analysis.

The trial can be terminated in the following circumstances: (1) occurrence of serious adverse events (AEs) related to the research medication, (2) the test drug is found to have no clinical value during the trial, (3) financial and management reasons, and/or (4) administrative authorities terminate the trial.

### Intervention

Eligible patients will be allocated to receive Xinyue capsule or placebo for 6 months in addition to conventional treatment, including antiplatelet, lipid-lowering, antihypertensive, or antidiabetic therapy, according to the clinical guidelines. The Xinyue capsules and placebo capsules (0.6 g ante cibum, three times daily for 24 weeks; China State Food and Drug Administration approval number Z20030073) will be provided by Jilin Jilin Jian Yisheng Pharmaceutical Co. Ltd. (Ji’An City, China). Each capsule is 0.3 g, equivalent to 50 mg of *P. quinquefolium* saponin. The Xinyue and placebo capsules have the same outer packaging, color, shape, and flavor.

### Outcomes and measures

The primary outcome is the time from randomization to the first occurrence of the major adverse cardiovascular event (MACE): cardiac death (any death unless an unequivocal noncardiac cause could be established), nonfatal MI (appearance of pathological Q waves that were absent at baseline or a total creatine kinase [CK] level more than two times the upper limit of normal [ULN] with presence of CK isoenzyme MB higher than the ULN), and urgent revascularization with either PCI or coronary artery bypass graft. The secondary outcome measures is the time from randomization to the first occurrence of, stroke, pulmonary embolism, and peripheral vascular events, as well as death due to any cause. Safety outcomes, which include a complete blood count, kidney and liver function tests, high-sensitivity C-reactive protein level, cardiac function index, blood lipid levels, Quality of Life Questionnaire (QLQ) score, 36-item Short Form Health Survey (SF-36) score, and TCM syndrome score will also be monitored periodically. All AEs will be followed from randomization to the end of the trial. Items to be measured and the time window of data collection are shown in Table 1.

**Table 1 Tab1:** Measurement items and points of data capture

	Screening	Treatment period			Follow-up period	
	Visit 1	Run-in period (visit 2)	12 weeks (visit 3)	24 weeks (visit 4)	12 weeks (visit 5)	24 weeks (visit 6)
Informed consent	X					
Inclusion/exclusion criteria		X				
Demographic data	X					
Medical history	X					
Concomitant medications	X					
Tongue and pulse condition in TCM	X	X	X	X	X	X
Vital signs	X	X	X	X	X	X
12-lead ECG	X			X		X
Complete blood count, urine and stool tests	X			X		X
Liver and renal function tests	X			X		X
Coagulation function test	X			X		X
Adverse event evaluation			X	X	X	X
Dispense drug		X	X	X	X	X
Primary endpoint			X	X	X	X
Secondary endpoint			X	X	X	X
Cardiac function	X			X		X
hs-CRP	X			X		X
Lipid panels	X			X		X
QLR score	X		X	X	X	X
SF-36 score	X		X	X	X	X
TCM syndrome score	X		X	X	X	X

*Abbreviations: ECG* electrocardiogram, *hs-CRP* high-sensitivity C-reactive protein, *SF36* 36-item Short Form Health Survey, *TCM* traditional Chinese medicine, *QLQ* quality of Life Questionnaire​

X represents the indicators tested in the specific time period

Coagulation function test: prothrombin time, activated partial thromboplastin time, fibrinogen, thrombin time

Lipid panels: high-density lipoprotein, low-density lipoprotein, cholesterol, triglycerides

Primary endpoint: time from randomization to the first occurrence of the major adverse cardiovascular event

Secondary endpoint: time from randomization to the first occurrence of stroke, pulmonary embolism, and peripheral vascular events, as well as death due to any cause

### Adverse events

AEs are defined as negative or unintended clinical manifestations following the treatment. Patients will be asked to report to the investigators any abnormal reactions occurring at any time during the trial. In addition, investigators will collect information about abnormal reactions monthly. All details of related and unexpected AEs, such as time of occurrence, degree of AE, and suspected causes, will be recorded on CRFs. There is also a data safety monitoring board to oversee the trial.

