### Study-specific visits and procedures

The schedule for all study-related procedures for all evaluations is shown in Table 1. For each procedure, subjects are to be assessed by the same investigator or site personnel whenever possible. The timing of each visit is relative to randomization (day 1). Baseline measures include demographic characteristics, medical history, medications, measurement of vital signs (temperature, blood pressure, breathing and heart rates), complete blood count, routine urine test, stool test, liver and kidney function tests, 12-lead electrocardiogram, cardiac ultrasound, TCM syndrome, and QLQ and SF-36 scores (details in the ​Additional file 2). All baseline measurements excluding the medical history will be repeated with all participants at visit 4 and visit 6. The TCM syndrome, QLQ, and SF-36 data will be recorded at visit 3 and visit 5. AEs and outcome measurements will be recorded from visit 3 to visit 6.

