### Statistical analysis

The data from all participating centers will be combined for statistical analysis of the primary and secondary endpoints as well as AEs. The analysis will be done at Beijing Jiaotong University. Continuous variables will be presented as the mean ± SD. The comparability of the characteristics between the two study groups will be assessed using a two-samples Student’s *t* test for continuous variables and the χ^2^ test or Wilcoxon test, when appropriate, for categorical variables. The Wilcoxon paired signed-rank test will be used for within-group comparisons.

All randomized patients constituted the intention-to-treat population. All participants will be analyzed according to their original treatment allocation. Primary and secondary endpoint data will be collected for the entire follow-up period for all patients. Patients lost to follow-up will be considered at risk until the date of last contact, at which point they will be censored. Kaplan-Meier curves will be used to examine MACE-free survival time. The Cox proportional hazards model with covariates of treatment will be used for primary and secondary analyses. Hazard ratios and 95 % confidence intervals for each of the categories determined by age, sex, diabetes, and conventional therapy will be provided for the primary and secondary endpoints.

For all analyses, a value of *P* < 0.05 will be considered statistically significant, and all tests will be two-tailed. All analyses will be conducted using SAS software version 9.2 (SAS Institute, Cary, NC, USA).

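### The Adverse events section ties CRF recording of event details to relatedness and expectedness, which does not fit the sections that follow, record and analyze all AEs

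*Protocol article*

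**What the plan says.** The Adverse events section of the protocol article starts broadly. Its definition is "AEs are defined as negative or unintended clinical manifestations following the treatment", with no condition on cause or expectedness. Patients have an open invitation to report: "Patients will be asked to report to the investigators any abnormal reactions occurring at any time during the trial". Investigators also enquire themselves: "investigators will collect information about abnormal reactions monthly". The section then says what is written down: "All details of related and unexpected AEs, such as time of occurrence, degree of AE, and suspected causes, will be recorded on CRFs".

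Three other places deal with AEs and set no such condition:

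- Outcomes and measures: "All AEs will be followed from randomization to the end of the trial". Table 1 in that section marks AE evaluation at visits 3 to 6.
- Study-specific visits and procedures: "AEs and outcome measurements will be recorded from visit 3 to visit 6".
- Statistical analysis: data from all centers are combined for "statistical analysis of the primary and secondary endpoints as well as AEs".

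The section on data entry and quality control makes the CRF the route by which center data reach the trial database.

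**The concern.** In a double-blind placebo-controlled trial, the soundest evidence on harm is the difference between randomized arms in all AEs. It does not depend on anyone judging correctly whether a particular event was caused by the capsules. A rule that makes recorded detail depend on that judgement gives up some of this protection. Events judged unrelated or expected may be counted without an onset date or a grade, or may be handled differently from site to site.

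Bleeding shows why this could matter here. The Intervention section lists antiplatelet drugs among the conventional treatment. A bleed is therefore an event that an investigator could readily attribute to background therapy or regard as expected. The Background reports that an earlier study of Xinyue with Chuanxiong capsules reduced events "without increasing the risk of major bleeding", so the authors know that bleeding is of interest in these patients. An analysis of AEs by severity or time of onset can use only what the CRF holds.

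**Working it through.** The article states no figure on this point, so the check is a comparison of texts.

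**Step 1. Scope of each statement.**

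| Section | Activity | Condition on the AE |
|---|---|---|
| Adverse events, definition | What counts as an AE | None |
| Adverse events, patient reports and monthly enquiry | Finding events | None |
| Adverse events, CRF sentence | Recording timing, grade and presumed cause | Related and unexpected |
| Outcomes and measures; Table 1 | Follow-up and evaluation | None |
| Study-specific visits and procedures | Recording at visits 3 to 6 | None |
| Statistical analysis | Pooled analysis | None |

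One row differs from the rest. It is also the only sentence in the article that says what AE content is entered on the CRF.

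**Step 2. What the phrase can mean.** It can be read as events that are both related and unexpected, or as related events together with unexpected events. Sorting AEs by the two judgements shows which have detail assured by the sentence:

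| Judged | Both conditions needed | Either condition enough |
|---|---|---|
| Related, unexpected | Yes | Yes |
| Related, expected | No | Yes |
| Unrelated, unexpected | No | Yes |
| Unrelated, expected | No | No |

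On either reading at least one group of events has no detail assured. A bleed attributed to antiplatelet therapy and regarded as expected on that therapy falls in the last row. If expectedness were judged against the study capsule instead, the same bleed could be unrelated but unexpected, and the two readings would treat it differently. The article does not say which standard applies.

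**Step 3. Do the other sections settle it?** They show an intention to follow, record and analyze all AEs. They do not say that timing and grade are entered for all of them. A site following the visit section and a site following the CRF sentence could both believe that they comply, and the trial has 25 centers.

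**Step 4. Size.** The loss would depend on how many AEs occur and what share is judged unrelated or expected. The article gives neither, so no figure can be derived.

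**The case against.** The strongest reply is that this is one loosely worded sentence in a condensed article. It says that certain events will be recorded in detail. It does not say that others will not be. The definition, the patient reports, the follow-up of all AEs, the visit recording and the pooled analysis all point to full coverage, and a data safety monitoring board oversees the trial. The sentence concerns detail fields, not whether an event is counted. The full protocol and the CRF may well be clear.

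Much of this stands, and it rules out several stronger readings that a reader might infer:

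- **That the CRFs capture nothing but related and unexpected events, so that most AEs are lost.** The text contains no such exclusion, and without event frequencies the word most has no basis.
- **That the safety comparison is biased between arms.** Care providers and attending physicians are blinded under Randomization and blinding, so their judgements should not differ systematically by arm. The likely harm is under-capture.
- **That monthly enquiry contradicts the 12-weekly visits.** The article presents the monthly enquiry as an addition to patient reports. It can run alongside formal evaluation at visits 3 to 6.
- **That leaving bleeding out of the safety list is an error.** The list is introduced as inclusive, a bleed meets the AE definition, and blood counts and coagulation tests are scheduled. A graded bleeding outcome may be left to the full protocol.

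The reply does not remove the inconsistency. The article did not merely leave the recording rule out. It stated one, and that rule is narrower than the other sections.

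**Conclusion.** The concern holds as an inconsistency within the article that should be fixed. The CRF sentence makes the recording of AE details depend on relatedness and expectedness, whereas the sections on follow-up, visit recording and analysis cover AEs without restriction. If sites apply the sentence literally, events judged unrelated or expected could lack onset and severity, and the blinded safety comparison would lose sensitivity.

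This conclusion rests on two assumptions: that at least some sites would follow the sentence as written, and that the full protocol or CRF does not already override it. The extent of the loss cannot be quantified from the documents. The primary endpoint is unaffected.

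**What to change.** Reword the CRF sentence in the Adverse events section along these lines: every adverse event and serious adverse event, whatever its relatedness or expectedness, is recorded on the CRF with date of onset, severity and outcome; the investigator's judgements of relatedness and expectedness are recorded as additional fields. In Statistical analysis, add that the comparison of AEs between the randomized arms is based on all AEs, with any analysis restricted to related events as a supplement.

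If the full protocol and CRF already work this way, correcting the article's sentence is enough. If they do not, the CRF and site instructions need the same change.

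The cost is a sentence or two of wording and somewhat more AE data entry. Trial status reports 452 of 1100 participants enrolled and no analysis done. At that point 1100 − 452 = 648 participants were still to come and would be covered from entry. For those already enrolled, sites could complete missing onset and severity from source records where these exist.

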### Study-specific visits and procedures

The schedule for all study-related procedures for all evaluations is shown in Table 1. For each procedure, subjects are to be assessed by the same investigator or site personnel whenever possible. The timing of each visit is relative to randomization (day 1). Baseline measures include demographic characteristics, medical history, medications, measurement of vital signs (temperature, blood pressure, breathing and heart rates), complete blood count, routine urine test, stool test, liver and kidney function tests, 12-lead electrocardiogram, cardiac ultrasound, TCM syndrome, and QLQ and SF-36 scores (details in the ​Additional file 2). All baseline measurements excluding the medical history will be repeated with all participants at visit 4 and visit 6. The TCM syndrome, QLQ, and SF-36 data will be recorded at visit 3 and visit 5. AEs and outcome measurements will be recorded from visit 3 to visit 6.

